### Publication

Results of the study will be published after approval by the clinical and scientific advisors, Principal Coordinating Investigators, and statistician in an international scientific journal and/or presented on international scientific meetings.

The Principal Investigators will provide the Ethics committee with a summary of the trials outcome, and if applicable the regulatory authorities with any reports required.

All publication will maintain data protection of patient data as well as data of the participating investigators.

### Time Schedule

Inclusion first patient (FPFV): 01.07.2007

Inclusion last patient (Randomization): 01.07.2010

Last patient out (LPLV): 01.07.2011

Database closure: 01.10.2011

Termination statistical analysis: 31.01.2012

Study report: 01.07.2012

## Discussion

Today, there is a trend towards the concept of "Damage Control Orthopedics" in the management of multiple trauma patients with long bone fractures. But, evidence from the current literature is insufficient. As discussed above, results are contradictory, a generalized management strategy is missing. Thus, in the era of "evidence-based medicine", there is the need for a more specific, clarifying randomized controlled trial. Therefore this new trial was initiated.

To our knowledge, this trial is the first to evaluate the risk adapted damage control orthopedic surgery of femur shaft fracutres in multiple trauma patients in a randomized controlled design. In 2003, Pape et al. [32] presented their results of a randomized controlled trial. They investigated the impact of intramedullary instrumentation versus damage control for femoral fractures on immunoinflammatory parameters and complications [32,33]. But, in contrast to this study, where a risk adaption is performed, they excluded multiple trauma patients with severe brain and thoracic injuries (AIS > 3) and patients in unstable or critical condition, too. In summary, the included patients were injured less severely. Furthermore, Pape et al. did not define criteria that must be fulfilled for performing the secondary definitive procedure. Therefore these two trials are not comparable in the authors' opinion.

Since there is still no clear evidence for the superiority of one of the strategies participation in the trial is not associated with an increased risk by itself. If one of the strategies proves superiority the benefit (reducing the organ failure) is evident. The main endpoint is a surrogate endpoint for mortality, i. e. the trial may lead to a definite treatment strategy in patients with multiple trauma lowering the overall mortality. If non-inferiority of the primary internal fixation can be proven, it can be assumed that hospital stay, number of operations etc. are lower in this group, thus lowering the expenses.

Although mortality would have been the most appreciated endpoint, a trial with mortality as the main endpoint would need approximately 1300 patients per arm. In addition to the fact that such a trial is almost undoable for practical reasons the concentration on mortality does not cover all aspects of the planned intervention since the damage control approach primarily tries to limit the sequelae of the "second hit" by surgical intervention. This is reflected by the measurement of organ failure by appointing maximum values for patients who died. The SOFA score has been developed for the sequential evaluation and description of organ failure and has been shown to be a suitable indicator of prognosis in trauma patients [29].

A significant effect may only be shown in a group of medium probability of death (20-60%), especially concerning maximum SOFA-score, as the type of procedure chosen in patient groups of very high or very low mortality will most likely have only a minimal effect on this endpoint.

Because the most important factors that determine prognosis in multiple trauma patients are considered, a comparison of this heterogenic patient collective is possible.

In the current literature, another facet of the optimal surgical treatment in multiple trauma patients is discussed: Biochemical/immunologic factors. It has been shown that the traumatic tissue damage stimulates a maximal activation of the immune system, which leads to its depletion and debilitation [34-36]. As a consequence of a failing immune system a systemic inflammatory response syndrome (SIRS) or sepsis can occur. Both are potentially life threatening complications, in the course of which all organ systems can be affected [34,37,38].

Some of the best analyzed pro-inflammatory cytokines are tumor necrosis factor (TNF)-α [39,40], and the interleukines (IL)-6 and IL-8 [41-43]. Circulating IL-6 is quickly detectable after trauma [42] and has been shown to correlate with trauma load [44].

But so far, the transfer of results into clinical context and the verification for potential decision making (therapy) with respect to risk reduction during secondary surgical procedures after trauma failed.

In extension to the clinical part of the present research a further investigation is planned to monitor both study groups for potential differences in immunofunction/-dysfunction as reflected by temporal patterns of selected circulating mediators and markers for immuno-competence. This approach may result in optimum individualized concepts for fracture repair depending on the patient's individual immuno-competence [45].

Nevertheless, the prerequisites for performing this study give rise to hope for answering the question whether the "early total care" or the „damage control” concept is associated with better outcome.

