### Proposed sample size/Power calculations

The primary hypothesis is that the damage control principle is able to reduce the extent of organ failure. Organ failure is measured daily by the SOFA score (five organs, excluding CNS, 0-4 points per organ). The maximum SOFA score during ICU stay is used as primary outcome measure. It is assumed that the maximum SOFA score could be reduced by 1-2 points. This corresponds to a reduction from "organ failure" to "organ dysfunction", or from "organ dysfunction" to "normal organ function" for one organ. Data from Ferreira et al. indicate that a 2 point increase in SOFA score correlates with an average 10% increase in mortality [29]. According to the database of the Deutsche Interdisziplinäre Vereinigung Intensivmedizin (DIVI; quality assessment in intensive care; 45.000 admissions 2000-2004) maximum SOFA score is about 3.2 ± 3.2 in a general ICU population, and 3.3 ± 3.1 in emergency admissions with trauma. Thus the estimated effect (1.5 points reduction) corresponds to a standardized effect size of 0.5. Assuming usual error rates (a = 0.05; b = 0.20), 64 patients per group would be required. However, due to the non-normal nature of the distribution and the use of non-parametric statistics, the number of patients to be randomized has to be increased by 10%. Thus, the total sample size is set to 140 patients (70 per group). Compliance and rate of loss to follow-up do not affect primary outcome measures.

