### Statistical analyses

The main outcome variable is the maximum SOFA score during ICU stay. In order to have comparable periods, the time period for SOFA score assessment is limited to the first 28 days after trauma. Documentation of daily SOFA scores is continued in intermediate care or other high dependency units.

The maximum SOFA score will be compared using non-parametric statistics (U-test) due to the substantial skewness of the distribution. Since severity of trauma is assumed to be a major determinant of outcome (including rate of organ failure) the comparability regarding Injury Severity Score (ISS) is tested before analysis. In case of substantial imbalance (p < 0.15; U-test) a stratified analysis of outcome will be performed (two groups; ISS ≤/> 30 points).

Analysis will be done according to intention to treat; regarding to the per protocol (PP) analysis we expect the PP-population to be 5% less.

There will be one interim analysis of data collection when about half of the expected sample size has been included (70 cases). The p-value for the interim analysis will be set at 0.005 so that the final analysis will be done at a significance level of 0.048, according to Fleming and O'Brien [31].

During interim and final analysis, a detailed safety analysis will be performed by comparing predicted and observed survival within each group and reviewing individual cases of non-survivors.

In addition, all secondary endpoints mentioned in the protocol will be considered for explorative analysis, because these factors are repeatedly named in the discussion about the advantages of damage control orthopedics. The aim of presenting all these data is not a confirmative statistical testing, but rather to serve as a basis for comparative analyses in future meta-analyses regarding damage control orthopedics versus early total care strategies.

The hospital perspective on costs includes the initial and all secondary operations or readmissions until one year after randomization. As most costs during hospital stay are caused by surgery itself and ICU care, data collection and statistical analysis will focus on these two aspects. The results will be reported as a cost-effectiveness analysis using life-years lost as the measure of treatment benefit. These analyses will employ decision-analytic models for the optimum management of multiply injured patients with femoral shaft fracture.

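### The Discussion treats non-inferiority of primary nailing as a provable result, but the hypothesis, sample size and test are all for superiority and no margin is given (minor; wording fix)

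*Protocol article*

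**What the plan says.** The Discussion sets out what the trial may show. After the case in which one strategy proves superior, it adds: "If non-inferiority of the primary internal fixation can be proven, it can be assumed that hospital stay, number of operations etc. are lower". The end of the sentence extends this to a saving for the primary fixation arm.

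The design sections are written for a different question:

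- **Hypothesis** (Proposed sample size/Power calculations): "The primary hypothesis is that the damage control principle is able to reduce the extent of organ failure".
- **Effect and sample size** (same section): "It is assumed that the maximum SOFA score could be reduced by 1-2 points". The calculation takes 1.5 points, read as half a standard deviation, and concludes: "Assuming usual error rates (a = 0.05; b = 0.20), 64 patients per group would be required". A 10% increase for the non-parametric test brings this to 70 per group, 140 in total.
- **Primary test** (Statistical analyses): "The maximum SOFA score will be compared using non-parametric statistics (U-test) due to the substantial skewness of the distribution". With one interim look, the final level is 0.048.
- **Resource use**: ICU and hospital stay, surgical interventions and costs of surgery are secondary endpoints. Statistical analyses makes the secondary endpoints exploratory and plans a cost-effectiveness analysis.

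No section of the article states a non-inferiority hypothesis, a margin, or a rule for judging non-inferiority from a confidence interval.

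**The concern.** A non-inferiority conclusion needs a margin fixed in advance and a sample size that matches it. These are design elements, because they determine how many patients are needed; they are not details normally left to an analysis plan. The article gives its hypothesis, sample-size reasoning and test, and all three concern superiority of damage control. The Discussion therefore holds out a conclusion that the stated design does not support.

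The sentence then moves from non-inferiority on organ failure to shorter stay, fewer operations and lower expenses by assumption. Non-inferiority on the maximum SOFA score does not imply shorter stay or lower expenses, and the trial measures these outcomes.

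At stake is how a null result is presented. With no margin in place, a non-significant U-test could be described afterwards as showing that primary nailing is no worse and cheaper, in patients with a predicted mortality of 20 to 60%.

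**Working it through.** **Inputs.** From Proposed sample size/Power calculations: design effect 1.5 points within an assumed range of 1 to 2; standardized effect 0.5, so an implied SD of 1.5/0.5 = 3.0; database SDs of 3.1 and 3.2 ("maximum SOFA score is about 3.2 ± 3.2 in a general ICU population, and 3.3 ± 3.1 in emergency admissions with trauma"); 70 per arm. From Statistical analyses: final level 0.048, so z = 1.977. The non-inferiority margins below are assumptions, since the article gives none. All figures are normal approximations for a difference in means; the planned test works on ranks.

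**1. The plan's own figure.** n per arm = 2 × (1.960 + 0.842)² × (3.0/1.5)² = 62.8, so 63; the t-test version gives 63.8, so 64. Then 64 × 1.10 = 70.4, in line with the stated 70 per group. A one-sided calculation gives about 50 and does not reproduce 64. The sample size is a two-sided superiority calculation.

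**2. Precision.** SE = SD × √(2/70). Half-width = 1.977 × SE.

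| SD | SE | Half-width (points) |
|---|---|---|
| 3.0 | 0.507 | 1.00 |
| 3.1 | 0.524 | 1.04 |
| 3.2 | 0.541 | 1.07 |

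**3. How often a real benefit of damage control is missed.** P(not significant) = Φ(1.977 − d/SE), with d the true benefit.

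| True benefit d | SD 3.0 | SD 3.2 |
|---|---|---|
| 0.5 | 84% | 85% |
| 1.0 | 50% | 55% |
| 1.5 | 16% | 21% |

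For d = 1.0 and SD 3.0: Φ(1.977 − 1.972) = 50%. A non-significant test is thus about as likely as not when nailing is truly worse by 1.0 point, so non-significance alone cannot establish non-inferiority.

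**4. Power for non-inferiority at 70 per arm.** With truly equal arms and one-sided 0.025, power = Φ(margin/SE − 1.960). The n per arm for 80% power is 2 × (1.960 + 0.842)² × (SD/margin)².

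| Assumed margin | Power at 70 per arm (SD 3.2 to 3.0) | n per arm for 80% (SD 3.0 to 3.2) |
|---|---|---|
| 0.5 | 15–17% | 566–643 |
| 0.75 | 28–32% | 252–286 |
| 1.0 | 46–51% | 142–161 |
| 1.5 | 79–84% | 63–72 |

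Among these margins, power is near 80% only at 1.5 points, which is the whole effect the trial is designed to detect.

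**5. Sensitivity: deaths scored 20.** Outcome measures assigns 20 points after death within 28 days. If a share p die and survivors have mean m and SD 3.1, then SD² = (1 − p) × 3.1² + p(1 − p)(20 − m)². Both p and m are assumptions.

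| p | m | SD | Half-width | Power at margin 1.0 |
|---|---|---|---|---|
| 20% | 8 | 5.5 | 1.9 | 19% |
| 40% | 10 | 5.5 | 1.8 | 19% |
| 20% | 3.3 | 7.2 | 2.4 | 13% |
| 40% | 3.3 | 8.5 | 2.9 | 10% |

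The SD depends strongly on these inputs, so the table shows direction only. A mean-based approximation is also poor for a score with a spike at 20.

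**The case against.** The sentence is conditional, sits in a Discussion paragraph about possible benefits, and speaks of non-inferiority being proven, which is not the same as inferring it from a null result. The section on statistical analyses plans no such conclusion. A confidence interval from the same data could also address the question, so a non-significant U-test is not the only route. All of this stands, and it limits the point to a sentence that the design does not back.

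On costs, the objection is largely right. Stay, operations and costs are measured, and the cost analysis covers operations and readmissions to one year. Fewer planned operations after primary nailing follows from the two-step nature of damage control, as the section on adverse events notes. What remains is that shorter stay and lower expenses are assumed in the Discussion although data will be available.

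A reader might go further and infer any of three things:

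- **That the plan intends to read a null result as non-inferiority.** No passage says so.
- **That a null result is the most likely outcome.** At the protocol's SDs, power at 1.5 points is 79 to 84%. The opposite claim needs an inflated SD that rests on survivor scores and death rates the article does not give.
- **That a treatment recommendation would follow.** The sentence draws only a resource inference.

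**Conclusion.** The sentence is wrong as written: it presents as provable something for which the article states no hypothesis, margin, criterion or sample size. At the protocol's own SD the interval half-width is about 1.0 point, a true 1.0-point benefit of damage control is missed 50 to 55% of the time, and non-inferiority power at an assumed 1.0-point margin is 46 to 51%. If deaths scored as 20 widen the SD, power at that margin falls further, by an amount the article does not allow one to fix. These figures rest on normal approximations, 70 evaluable patients per arm and, for non-inferiority, truly equal arms. Confidence is high that the margin is absent and the design is for superiority. Severity is minor, because the primary superiority analysis, its level and its sample size are untouched.

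**What to change.** 1. Delete the non-inferiority sentence from the Discussion.
2. State that the treatment difference will be reported with its confidence interval, by a method suited to the skewed score, and that a non-significant primary test will be reported as inconclusive, not as non-inferiority.
3. Base any statement on hospital stay, number of operations or expenses on the secondary endpoints and cost analysis already planned.

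Do not rescue the sentence with a 1.5-point margin: that would accept primary nailing despite a loss of almost the full hypothesised benefit. A smaller margin would need its own justification and a larger trial; at 1.0 point, 142 to 161 per arm (284 to 322 in total against 140).

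Cost: wording only. One foreshadowed conclusion becomes unavailable; no test, level or patient number changes.

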## Abbreviations

AE: adverse event; AIS: abbreviated injury scale; ARDS: adult respiratory distress syndrome; BE: base excess; CNS: central nervous system; CRF: case report form; CT: computer tomography; DIVI: Deutsche Interdisziplinäre Vereinigung Intensivmedizin; DSMB: data safety monitoring board; DCO: damage control orthopedics; ETC: early total care; GCP: good clinical practice; GCS: Glasgow coma scale; GOS: Glasgow outcome scale; ICU: intensive care unit; ISS: injury severity score; KKSK: coordinating center for clinical studies Cologne; MODS: multi organ dysfunction syndrome; MOF: multi organ failure; OF: organ failure; PI: primary investigator (principle coordinating investigator); RISC: revised injury severity classification; SAE: serious adverse event; SIRS: systemic inflammatory response syndrome; SOFA: sepsis-related organ failure assessment; TISS: therapeutic intervention scoring system; TRISS: Trauma Injury Severity Score.

